## Abstract

**Background:**

Diabetic retinopathy screening (DRS) leads to the earlier detection of retinopathy and treatment that can prevent or delay the development of diabetes-related blindness. However, uptake continues to be sub-optimal in many countries, including Ireland. Routine management of type 2 diabetes largely takes place in primary care. As such, there may be an opportunity in primary care to introduce interventions to improve DRS uptake. However, few studies test the feasibility of interventions to enhance DRS uptake in this context. Our aim is to investigate the feasibility of an implementation intervention (IDEAs (Improving Diabetes Eye screening Attendance)) delivered in general practice to improve the uptake of the national DRS programme, RetinaScreen.

**Methods:**

The IDEAs study is a cluster randomised pilot trial with an embedded process evaluation and economic evaluation. Following stratification by practice size, eight general practices (clusters) will be randomly allocated to intervention (*n* = 4) or wait-list control groups (*n* = 4). The intervention will be delivered for 6 months, after which, it will be administered to wait-list control practices. The intervention is multi-faceted and comprises provider-level components (training, audit and feedback, health care professional prompt, reimbursement) and patient-level components (GP-endorsed reminder with information leaflet delivered opportunistically face-to-face, and systematically by phone and letter). Patient inclusion criteria are type 1 or type 2 diabetes and DRS programme non-attendance. A multi-method approach will be used to determine screening uptake, evaluate the trial and study procedures and examine the acceptability and feasibility of the intervention from staff and patient perspectives. Quantitative and qualitative data will be collected on intervention uptake and delivery, research processes and outcomes. Data will be collected at the practice, health professional and patient level. A partial economic evaluation will be conducted to estimate the cost of delivering the implementation intervention in general practice. Formal continuation criteria will be used to determine whether IDEAs should progress to a definitive trial.

**Discussion:**

Findings will determine whether IDEAsis feasible and acceptable and will be used to refine the intervention and study procedures. A definitive trial will determine whether IDEAs is a cost-effective intervention to improve DRS uptake and reduce diabetes-related blindness.

**Trial registration:**

ClinicalTrials.gov NCT03901898. Registered 3rd April 2019,

## Background

Diabetes mellitus (diabetes) places a significant burden on health systems, largely attributable to the complications associated with the condition [1, 2]. The number of people with diabetes is growing worldwide, with type 2 diabetes accounting for approximately 90% of all cases [2]. Diabetic retinopathy (DR) is the most common microvascular complication of diabetes and a leading cause of blindness among people of working age in many countries [3, 4], including Ireland [5]. Worldwide, it is estimated that approximately 28 million individuals have vision-threatening retinopathy [6]. Visual impairment due to retinopathy can negatively impact on an individual’s quality of life and ability to self-manage which can lead to other complications [7].

Diabetic retinopathy screening (DRS) leads to earlier detection of pre-symptomatic retinopathy and treatment to prevent or delay the development of diabetes-related blindness. Screening for retinopathy is effective in reducing the risk of vision loss [8] and is cost-effective [9, 10]. National and international guidelines recommend annual DRS for people with diabetes [11–13]. Despite evidence for the effectiveness of DRS, uptake continues to be sub-optimal in many countries [14–17]. The current uptake of the national DRS programme in Ireland, in operation since 2015, is approximately 56% [18]. In England, where a national DRS programme has been established for > 10 years, attendance rates vary from 71–91% [19, 20]. Non-attendance for screening has been identified as a risk factor for poor visual outcomes among those with diabetes [21]. Non-attendance is also costly for the health service; retrospective analysis of 1 year of missed appointments within a primary care organisation in the UK was calculated to cost £78,259 [22].

A range of individual factors are consistently highlighted as being associated with DRS attendance; younger age [23, 24], social deprivation [24–27], longer duration of diabetes, type 1 diabetes [24], poorer glycaemic control, smoking and hypertension [28] and lack of awareness of DR and the risk [28, 29]. However, health care professional and system-level factors also play a part. For example, the accessibility of screening centres, time to attend DRS and competing demands have been identified as barriers [29]. On the other hand, communication and trust between health care professionals and patients, including a recommendation to attend screening from a primary care professional, is an important enabler [28, 29]. As most of the routine management of type 2 diabetes takes place in primary care, it is arguably the best setting for interventions to improve uptake of DRS.

An ‘implementation intervention’ is a type of intervention which supports *implementation* of a clinical programme, for example, DRS uptake; the intervention may be a multi-faceted approach comprising a number of different implementation strategies [30]. Interventions may be more successful if they are theory-informed, target known barriers and enablers of attendance [19, 31, 32] and operate at multiple levels (i.e., system, professional and patient) [33–36]. Interventions to improve screening attendance can be effective [37–39] and often include patient education to increase awareness of diabetic retinopathy and/or patient reminders, or registration and reminder systems to support professionals to follow-up patients [38]. Though these approaches can improve DRS uptake, few which target *both* professionals and patients [14, 40–44] focus on primary care [14]. There are challenges associated with introducing complex interventions in the primary care setting [45]. Interventions are not always a good fit for the context in which they are used or do not align with stakeholder preferences [46]. It is important, therefore, not only to develop a multi-level intervention informed by theory and guided by local stakeholder input [47], but to test whether it is feasible to deliver in the real-world primary care setting.

## Aims and objectives

The main aim of the IDEAs (Improving Diabetes Eye screening Attendance) study is to investigate the feasibility of a multifaceted implementation intervention in primary care to improve the uptake of the national DRS programme, RetinaScreen. The intervention was developed through a multi-stage process, combining theory, consultation with multiple stakeholders and existing evidence. In line with Medical Research Council guidance [31], the study will address uncertainties about feasibility, economic evaluation and the study procedures. Specifically, it will address the following questions:
Are the intervention content, delivery and procedures acceptable to people with diabetes who will receive it and staff who will deliver the intervention?Is the intervention feasible to deliver in primary care practice and is fidelity achieved (i.e., intervention delivered as intended)?Are the data collection processes, including mode and duration of data collection and outcome measures used, acceptable to staff?Is the study feasible in terms of recruitment and retention procedures and data collection?What are the costs associated with the intervention?Do the results suggest that the intervention increases the uptake of DRS?

## Methods/design

### National screening programme

In Ireland, a national DRS programme (RetinaScreen) was introduced in 2013 to offer free, regular diabetic retinopathy screening to people with diabetes. All people with diabetes who are older than 12 years old are invited by letter to participate in the programme [48], after which they provide consent for the programme to hold and use their contact details and receive an appointment. People have their screening appointment at one of the designated screening centres in a variety of community locations, including high street opticians, community health care centres and community hospitals. Some screening locations based within primary healthcare centres are co-located with other services, including general practice. In Ireland, GPs are not trained and funded to screen for DR. Following screening, participants who require further investigation and treatment are referred to one of seven treatment clinics nationally. The national programme works in conjunction with photography and grading providers (EMIS Care and Global Vision) to deliver the service*.* There is no national register of people with diabetes. The initial RetinaScreen register was populated in 2012 by using information from national health schemes. Those who were not captured by this method have to be added to the register by a GP or by other healthcare professionals involved in diabetes care. It is estimated that between 5.6 and 5.8% of the population of Ireland have diabetes, and this would equate to approximately 200,000 patients having the condition across Ireland. Based on figures reported by the national programme, as of December 2017, there were 164,569 men and women on the register, approx. 82% of the estimated population. Figure 1 illustrates the process of consenting and attending the programme.

**Fig. 1 Fig1:**
[figure not shown]
Flow diagram illustrating the process of consenting to and attending the programme [48]

### Study design

IDEAs is a cluster randomised pilot trial [49], with an embedded process evaluation and a partial economic evaluation (cost analysis). Eight general practices (clusters) will be randomly allocated to intervention (*n* = 4) or waitlist control (*n* = 4) groups following stratification by practice size. Practices in the wait-list control group will be offered access to the intervention material and support the following pilot trial completion at 6 months. Data from the trial will be analysed and reported in accordance with the CONSORT criteria. The results of the pilot trial will inform the design of a large cluster randomized trial that will be powered to test the effectiveness of the intervention on DRS uptake. Continuation criteria, based on quantitative and qualitative process evaluation data, will be used to inform the decision about whether the intervention should be further evaluated as part of a full-scale randomised controlled trial (Table 1).

**Table 1 Tab1:** Summary of continuation criteria

^a^Continuation criteria	Measures used	Assessment of whether criteria have been met
Feasibility to recruit and retain practices.	• Number of practices responding to a call for Expression of Interest^b^ • Practice retention rates	If > 50 general practices within 2 months respond to call, then it is likely to proceed to full trial (*green*). If < 40 practices respond to call, then progression is unlikely to be feasible (*red*). If 40–50 practices respond within 2 month, then the Trial Steering Committee (TSC) will consider the feasibility of proceeding to the full-scale trial (*amber*) based on taking steps to improve response rate. If 8 practices are retained throughout a 6-month intervention period, then it is likely to proceed (*green*). If < 5 practices are retained, then a full-scale trial is unlikely to be feasible (*red*). If 5–7 practices are retained throughout the intervention period, then the TSC will consider feasibility of proceeding (*amber*) based on taking steps to improve retention.
Intervention is implemented as planned; that is, audit and feedback, addition of electronic prompts and delivery of a reminder in any format and receipt of intervention by eligible population of people with diabetes in participating practices	• Exploration of implementation fidelity during practice staff and patient interviews • Practice self-report during research support phone calls • Percentage of eligible patients receiving intervention based on practice audit data	If all core intervention components (audit, prompts, reminders) have been delivered by > 75% of practices, then it is likely to proceed to full trial (*green*) subject to review of qualitative data. If < 50% have delivered components, then it is unlikely to proceed (*red*). If 50–75% have delivered core components, then the TSC will consider the feasibility of proceeding (*amber*). The TSC will consider both the quantitative and qualitative data to judge whether the intervention is has been implemented.
Intervention is acceptable to patients and practice staff	• Percentages of staff reporting acceptability of intervention on self-report questionnaire. • Issues regarding acceptability of the intervention explored in qualitative interviews with staff and patients	If the intervention is acceptable to > 75% practice staff, then it is likely to proceed to full trial subject to review of qualitative data (*green*). If intervention is acceptable to < 50% staff, then it is unlikely to proceed (*red*). If the intervention is acceptable to 50–75% staff, then TSC will consider feasibility of proceeding (*amber*). The TSC will consider the quantitative and qualitative data and make an overall judgement on whether the intervention is acceptable.
Intervention has potential effect on screening uptake and demonstrates potential cost savings which are likely to outweigh the direct cost of implementing the intervention; specifically, the intervention (1) increases the absolute number of patients registered for diabetic retinopathy screening and (2) increases the absolute number of patients attending or intending to attend screening, measured descriptively	• Number registered for diabetic retinopathy screening based on practice audit data • Number attending or intending to attend based on practice audit data • Potential savings calculated based on cost of delivering intervention compared to control, and absolute increases in number attending or intending to attend	The TSC will judge whether the intervention has some positive impact and demonstrates cost savings.

^a^Continuation criteria are in place to facilitate the Trial Steering Committee (TSC) to assess whether it would be viable to progress to a full trial or whether this could be done following modifications to the trial protocol [50]. Continuation to the full trial will not occur unless problems can be overcome. Continuation criteria may be adapted, and supplementary data may be used to facilitate decision-making about whether to proceed to a full trial even when criteria have not been met

^b^To achieve 80% power to detect a change from 60 to 70% (*α* = 0.05), a total sample of 712 eligible patients would be needed. Assuming an average practice size of 1200 patients and a 5% prevalence of type 2 diabetes, at each practice, it is estimated that 12 patients would not be registered for the screening programme (20%). Of the 48 patients registered, 18 would be eligible (17 would be non-consenters (34%) and 1 would be a non-attender (3%)). Therefore, at least 40 practices would need to be recruited (20 per arm) for a full trial. To allow for a lower number of eligible patients per practice, we aim to recruit > 40 practices for the full trial

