#### People with diabetes

Inclusion criteria include the following:
Aged 18 years or overHave diagnosed diabetes (type 1 or type 2)Are eligible to attend the national screening programme but have not attended the screening service (i.e., recently in the past 12 months or ever)

Individuals will be excluded if they have attended the DRS programme recently (i.e., in the last 12 months) or are known to be having retinopathy treatment.

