### Sample size

As this is a pilot trial, formal sample size calculation has not been carried out [51]. The purpose of the pilot is to investigate the feasibility and acceptability of the intervention and study procedures with a view to adapting these, if necessary, for a future definitive trial. Eight practices will be recruited. Based on previous work conducted by the research team, within a practice, it is expected that 20% of patients will not be registered. Of those who are registered, it is expected 34% will not have consented to the programme, and 3% will not have attended. Therefore, assuming an average practice size of 1200 patients and a 5% prevalence of type 2 diabetes, at each practice, it is estimated that 12 patients would not be registered for the screening programme (20%). Of the 48 patients registered, 18 would be eligible (17 would be non-consenters (34%) and 1 would be a non-attender (3%)).

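### The definitive-trial calculation uses a change from 60% to 70% with no named outcome or population, and no support for that rate in the non-attenders to whom it is applied

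*Protocol article*

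**What the plan says.** The calculation is in footnote b to Table 1 (Study design) and is attached to the first continuation criterion, on recruiting practices. It is set up "To achieve 80% power to detect a change from 60 to 70" per cent with α = 0.05, and concludes that "a total sample of 712 eligible patients would be needed". Neither the outcome nor the group in which the 60% is expected is named.

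The conversion to practices starts from 1200 patients per practice and 5% prevalence, so 60 people with diabetes, of whom 12 are unregistered and 48 registered. Of the registered, 18 are counted as eligible: 17 non-consenters and 1 non-attender. The Sample size section repeats the basis: "Of those who are registered, it is expected 34% will not have consented to the programme, and 3% will not have attended". The footnote concludes that "at least 40 practices would need to be recruited (20 per arm) for a full trial".

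The criterion calls fewer than 40 responding practices red, 40 to 50 amber and more than 50 green.

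The inclusion criteria (People with diabetes) admit those who "have not attended the screening service (i.e., recently in the past 12 months or ever"), and attendance in the last 12 months is an exclusion. The Background puts national programme uptake at about 56%.

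**The concern.** A two-proportion calculation needs the expected control-arm rate, at follow-up, in the patients who will be compared. Here those patients were selected because they had not attended. Taken as attendance, a control rate of 60% would mean that three in five of them attend within the follow-up period without the intervention. The protocol offers no evidence for this.

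At stake is more than a figure for a later trial. Forty practices is also the red/amber boundary that the steering committee will apply in this pilot. If the rate does not belong to the patients analysed, neither the practice number nor the cut-offs that appear to be built on it have a stated basis.

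**Working it through.** **Inputs from the protocol:** 60% and 70%, power 80%, α = 0.05 (sidedness not stated; two-sided reproduces the result), 1:1 allocation, 18 eligible patients per practice.

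**Assumptions made here, because the protocol gives no values:** control-arm rate among eligible patients 5% to 30%; a 10-point difference; intracluster correlation (ICC) 0.05.

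**1. Reproduce the stated figure.** Pooled-variance formula, no continuity correction:

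n per arm = [1.960·√(2·p̄·(1−p̄)) + 0.842·√(p₁(1−p₁) + p₂(1−p₂))]² / (p₂−p₁)²

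With p₁ = 0.60, p₂ = 0.70, p̄ = 0.65: [1.960·√0.455 + 0.842·√0.45]² / 0.01 = 355.9, so 356 per arm and 712 in total. This matches exactly.

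**2. Reproduce the practice number.** 37% of 48 is 17.8, taken as 18. 712/18 = 39.6, so 40. The step goes straight from patients to practices, so the design effect is implicitly 1.

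**3. What does 60% resemble?** On the footnote's counts, 48 − 18 = 30 registered patients are not eligible. 30/48 = 62.5% of registered patients, and 30/60 = 50% of all patients with diabetes. National uptake is about 56%. The rate lies close to wider-population uptake but equals none of these.

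**4. The same 10-point difference at other control rates.** Design effect = 1 + (18 − 1)·0.05 = 1.85.

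| Control vs intervention | Total, no clustering | Practices at 18 each | Total × 1.85 | Practices at 18 each |
|---|---|---|---|---|
| 5% vs 15% | 282 | 16 | 522 | 29 |
| 10% vs 20% | 398 | 23 | 737 | 41 |
| 20% vs 30% | 588 | 33 | 1088 | 61 |
| 30% vs 40% | 712 | 40 | 1318 | 74 |
| 60% vs 70% (as stated) | 712 | 40 | 1318 | 74 |

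The third and fifth columns are the totals divided by 18 and rounded up. The 30% vs 40% row equals the stated one because the variance is symmetric about 50%.

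**5. A different effect scale.** The odds ratio for 60% vs 70% is (0.7/0.3)/(0.6/0.4) = 1.56. Holding that ratio instead of the 10 points gives, before clustering, 2804 patients at a 5% control rate, 1516 at 10% and 894 at 20%. A lower control rate then raises the requirement.

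**The case against.** **It is a pilot, and the figure is provisional.** The eight practices, the randomisation and the descriptive analysis do not depend on footnote b. The Analysis section says pilot data will supply parameters for the definitive sample size, and footnote a allows the criteria to be adapted. This stands and limits the consequence. It does not repair the cut-offs, which are to be applied before those parameters exist.

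**60% may have been meant for a wider outcome.** The fourth criterion counts patients attending or intending to attend, and such a rate could be higher than attendance alone. This is possible, but the footnote does not say so, and no control-arm value is given for that measure either.

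**The plan already aims above 40 practices.** It does, but the reason given is fewer eligible patients per practice, not clustering.

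**Stronger readings a reader might infer, which the document does not support:**

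- *That 60% is the uptake of registered patients, wrongly carried over.* It is a reasonable inference, but the protocol never labels the rate. Reading it that way would give 712/48 = 14.8, so 15 practices, or 712/60 = 11.9, so 12, depending on a denominator the reader has to choose.
- *That the control rate must be 0%, since all are non-attenders.* Non-attendance at entry covers the past 12 months; some patients may have attended earlier. The formula needs the rate at follow-up, which entry status does not fix.
- *That 712 or 40 is too large, or too small.* The table shows 40 practices inside the plausible range. At 10% vs 20% with an ICC of 0.05 the answer is 41.
- *That there is an arithmetic slip.* There is none.

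**Conclusion.** The point holds as a fault in an input. The protocol takes a control rate of 60%, attaches it to no outcome or population, and applies the result to patients in whom nothing in the document supports that rate. It also makes no clustering allowance for a trial it describes as cluster randomised. The 40-practice figure, and the cut-offs of below 40, 40 to 50 and above 50 that it appears to underlie, therefore lack a justified basis.

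The size of the uncertainty is about 16 to 40 practices before clustering and 29 to 74 with it. This rests on assumed control rates of 5% to 30%, a 10-point difference, an ICC of 0.05 and the protocol's own 18 eligible patients per practice. The direction of the error is not established. The link between the 40 practices and the cut-offs is inferred from the matching number and from the footnote being attached to that criterion.

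**What to change.** Rewrite footnote b so that it:

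1. names the outcome to which the rates apply: attendance, or attending or intending to attend;
2. states an assumed 6-month control-arm rate and a target difference among eligible non-attenders, labelled as assumptions;
3. shows the totals and practice numbers over a range of control rates and ICCs, with the design effect written out.

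Then restate the cut-offs of the recruitment criterion from that range, and mark both the practice number and the cut-offs as provisional until the pilot's control-arm estimate is available. That estimate will itself be imprecise: four control practices at 18 patients is about 72 people.

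Do not solve the problem by redefining the outcome over all registered patients. Recent attenders are excluded, and the 6-month re-audit covers eligible patients only, so that route would change eligibility and data collection.

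The cost is a revised footnote and criterion wording. Eligibility, the eight pilot practices, data collection and the descriptive analysis are untouched. The stated practice number and cut-offs may change.

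### The 40-practice figure behind the recruitment continuation criterion has no allowance for clustering, although the definitive trial is cluster randomised

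*Protocol article*

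**What the plan says.** Under Study design, the protocol article says the pilot will inform a "large cluster randomized trial that will be powered to test the effectiveness of the intervention on DRS uptake". Table 1 sets the recruitment continuation criterion by the number of practices that answer a call for expressions of interest: fewer than 40 is red, 40 to 50 is amber, and above 50 is green ("If > 50 general practices within 2 months respond to call, then it is likely to proceed to full trial").

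Footnote b, attached to that measure, gives the reasoning. It begins "To achieve 80% power to detect a change from 60 to 70" percent at α = 0.05, and states that "a total sample of 712 eligible patients would be needed". It then takes 18 eligible patients per practice (17 non-consenters and 1 non-attender among 48 registered) and concludes: "Therefore, at least 40 practices would need to be recruited (20 per arm) for a full trial". The one reason it gives for going above 40 is that practices may have fewer eligible patients than assumed.

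The Quantitative analysis section says the pilot will supply parameters for the later sample size and names the mean, the standard deviation and the intervention effect. No ICC or design effect appears in the article.

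**The concern.** Patients in the same practice tend to resemble one another in whether they take up screening, because they share staff, systems and access to screening sites. When practices are randomised, the number of patients needed is that for individual randomisation multiplied by 1 + (m − 1) × ICC, where m is the number of patients analysed per practice. Footnote b appears to omit this step.

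This is not a detail left to another document. The article prints the full calculation and its conclusion, and uses the result as a decision boundary of the present pilot. If 40 practices do not deliver the stated 80% power, the steering committee will judge recruitment feasibility against too low a number. A result in the amber range would also prompt efforts to raise the response towards the wrong target.

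**Working it through.** **Inputs from footnote b:** 60% v 70%; α = 0.05 (sidedness not stated); 80% power; m = 18; equal arms. **Assumed, because not given:** ICC of 0.01, 0.02, 0.05 or 0.10, and equal cluster sizes.

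**1. Reproduce 712.** Pooled two-proportion formula, two-sided:

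n per arm = [1.960 × √(2 × 0.65 × 0.35) + 0.8416 × √(0.60 × 0.40 + 0.70 × 0.30)]² / 0.10²
= [1.960 × 0.67454 + 0.8416 × 0.67082]² / 0.01 = 355.9, rounded up to 356.

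The total is 2 × 356 = 712, an exact match. A one-sided test gives 562 and a continuity correction gives 752, so the printed figure is the plain two-sided one with a design effect of 1.

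**2. Reproduce 40.** 712 / 18 = 39.6, rounded up to 40. Forty practices hold 40 × 18 = 720 patients, 8 more than needed.

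**3. ICC at which 80% power is still met.** Set K × m / 712 = 1 + (m − 1) × ICC:

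- 40 practices: (720/712 − 1) / 17 = 0.0007
- 51 practices: (918/712 − 1) / 17 = 0.017
- 52 practices (smallest equal split above 50): (936/712 − 1) / 17 = 0.0185

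**4. Practices needed and power.** Design effect DE = 1 + 17 × ICC. Practices needed = 712 × DE / 18, rounded up to an even number. Power = Φ{[0.10 × √n − 1.960 × 0.67454] / 0.67082}, with n = (K × 18 / 2) / DE per arm.

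| ICC | DE | 712 × DE / 18 | Practices needed | Power, 40 practices | Power, 51 practices |
|---|---|---|---|---|---|
| 0.01 | 1.17 | 46.3 | 48 | 74% | 84% |
| 0.02 | 1.34 | 53.004 | 54 | 68% | 78% |
| 0.05 | 1.85 | 73.2 | 74 | 54% | 65% |
| 0.10 | 2.70 | 106.8 | 108 | 40% | 49% |

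Example for 51 practices at ICC 0.02: n = 459 / 1.34 = 342.5 and √342.5 = 18.51, so (1.851 − 1.322) / 0.6708 = 0.788 and Φ = 0.785 (0.7847, shown as 78%). With 52 practices the four powers are 84%, 79%, 66% and 50%.

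**5. Sensitivity to cluster size.** Footnote b leaves out the 12 unregistered patients per practice. If they counted, m = 18 + 12 = 30 and DE = 1 + 29 × ICC. Forty practices would then hold 80% power up to an ICC of (1200/712 − 1) / 29 = 0.024, and 51 up to (1530/712 − 1) / 29 = 0.040. Power with 40 practices would be 89%, 82%, 64% and 45% over the same four ICCs.

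**The case against.** Several points can be made for the plan.

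- **The threshold is not binding.** Green means only that progression is likely. Footnote a of Table 1 lets the committee adapt the criteria, and the definitive sample size is to be recalculated from pilot data. This stands as mitigation, but it does not correct the printed figure. Discretion gives no prompt to question a green result, and the parameters listed for the recalculation do not include an ICC.
- **Green is above 40, which may absorb clustering.** It does so in part: 51 practices reach 80% for an ICC up to about 0.017. A reader might infer that all three cut-offs are built on 40, or that 51 practices fall short at any plausible ICC. The document supports neither. Only the red/amber boundary equals 40, the cut-off of 50 is not derived, and no ICC is given. Equally, the margin cannot be claimed as a clustering allowance, because the only stated reason for exceeding 40 is fewer eligible patients per practice.
- **Eighteen may be too low.** The patient inclusion criteria appear to admit unregistered patients, and registration is itself an outcome. With 30 per practice the shortfall shrinks, as shown in the working. This makes the size conditional. However, the footnote divides by 18, and even at 30 power falls below 80% at an ICC of 0.05.
- **Responders are not the definitive sample.** This is correct. A reader might want to subtract the eight pilot practices from the count, but nothing confines the definitive trial to practices answering this one call, so that subtraction is not required.
- **The pilot needs no power calculation.** True, and not in dispute. The point concerns the definitive-trial figure used as a pilot criterion.

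**Conclusion.** The point holds. The 712 patients and 40 practices are individually randomised figures applied to a trial that will randomise practices. With the document's own 18 patients per practice, the stated 80% power fails at 40 practices for any ICC above about 0.0007. The shortfall depends on an ICC that the document does not give: power is 74% at 0.01 and 40% at 0.10.

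For the green cut-off the conclusion is weaker. A count just above 50 is adequate if the ICC is about 0.017 or less and every responding practice is eligible, joins and yields 18 patients; otherwise it can point to an underpowered trial. These figures assume equal cluster sizes. The pilot's own descriptive results are unaffected.

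**What to change.** 1. Restate footnote b with the design effect 1 + (m − 1) × ICC over a stated ICC range. Give either the corrected number of practices or the power that 40 practices actually provide. State whether m includes unregistered patients.
2. Re-anchor the red, amber and green cut-offs on the corrected number, and say how the green cut-off was reached.
3. Count only responding practices that meet the eligibility criteria in the recruitment section (an electronic health record system and a practice nurse).

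The cost is one recalculation and an amendment to the wording of Table 1; no extra pilot data are needed. The drawback is a less favourable stated figure: more practices or lower power.
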